### Secondary outcome measures

In a simulated scenario, in which the Reference-GA (R) is unknown, two groups will be randomly assigned from the complete database in order to compare differences among the Reference-GA (R), the GA obtained through the preemie-test (T) and the GA calculated by the comparators. Figure 1 presents such subgroups and measures for comparison.To monitor the device’s safety when in regular use by participants over a 72-hours period. Adverse events will be monitored, according to ISO 14155:2011 standards. This means any unexpected medical events, unintended disease or injury or unfortunate clinical signs in subjects, users or other people, whether related to the investigational medical device or not.To establish the *ease of use* of the preemie-test measurement as a potential method for preterm newborn diagnosis.

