### Eligibility criteria and participant’s timeline

A prospective sequential and concurrent enrollment process will select newborns in referral hospitals centres for neonatal care. Infants are eligible with the following inclusion criteria: (1) alive newborn; (2) enrollment during first 24 hours of life; (3) be 24 weeks or more of GA, at birth; (4) fetus underwent an obstetric ultrasound assessment before 14 weeks of pregnancy and (5) fetus also had obstetric ultrasound assessment between 14 and 22 gestational weeks. Exclusion criteria are: (1) malformation with structural skin alterations and (2) skin modifiers: anhydramnios, hydrops, congenital skin diseases or chorioamnionitis. Randomisation was not appropriate to assess the agreement between different methods to assess pregnancy dating.

In a nested case–control study, we will select newborns within the first 72 hours of life, discharge or death, whichever occurs first, with the following inclusion criteria: (1) RDS or (2) tachypnoea of the newborn (TTN) diagnosis. Ranges of GA will randomly pair controls. Exclusion criteria include: (1) the existence of extra pulmonary conditions with tachypnoea not due to prematurity and (2) diagnosis of Clinical or Laboratory-Confirmed Bloodstream Infection.

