### Sampling and sample size

The sample size calculation is estimated based on the primary endpoint. To test the hypothesis of equivalence between the preemie-test GA and the comparators GA, a sample of 787 subjects is necessary to detect an effect size of 10%. Using the G-Power 3.1 software,^20^ we assumed an alpha error of 0.05 and a power of test of 0.80 to support a paired t-test.

Sampling intends to arrange three groups of GA enrolment to preserve enough premature newborns with 3:2:1 proportion, similar to Wilson *et al*^21^: 392 term newborns, 263 premature newborns from 32 to 36 weeks and 6 days of GA and 132 extremely premature newborns from 24 to 31 weeks and 6 days of GA.

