### Data analysis

Demographics and baseline characteristics of the study group, as well the intervention measurements, will be summarised by the frequencies and the mean and standard deviation (SD), whereas the median and interquartile range (IQR) will be preferred for non-normally distributed continuous variables.

To model the GA prediction, computational randomisation will select two subsamples in the database. One of them to train the prediction model of GA based on skin reflectance and clinical variables, such as sex, time in an incubator, phototherapy, birth weight, among others. Another part will be for the analytical validation of the predictive model. Improvements in the existing prediction models for GA (preemie-test), will be conducted with conventional statistical and data mining analyses.

Regarding the primary endpoint, the agreement among three methods for GA will be calculated using the Intraclass coefficient correlation and Bland & Altman plots,^23^ and paired t-testing. The accuracy of the preemie-test in identifying the premature newborn, within a 1-week margin of error, will be the target of the accuracy analysis.

The relationship between the measurement of the newborn’s skin reflectance and complications due to pulmonary distress associated with immaturity will be evaluated by means of association tests and risk. The significance level for hypothesis tests will be 5%, together with 95% CIs.

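### The secondary comparison against the reference age splits infants at random into two groups, although every infant has R, T and C1 and the errors can be compared within the infant

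*Protocol article*

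**What the plan says.** Under Secondary outcome measures, the protocol describes a simulated scenario in which R is unknown. For it, "two groups will be randomly assigned from the complete database in order to compare differences among the Reference-GA (R"), and the sentence goes on to name T and the comparators. No reason or allocation ratio is given for the split. The layout is left to the figure: "Figure 1 presents such subgroups and measures for comparison". That figure is not reproduced in the text at hand.

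Other sections show which measures each infant has:

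- **R.** Eligibility requires that the "fetus underwent an obstetric ultrasound assessment before 14 weeks of pregnancy". The section on gestational age methods derives R from that scan.
- **C1.** Eligibility also requires that the "fetus also had obstetric ultrasound assessment between 14 and 22 gestational weeks". C1 comes from that window.
- **T.** The intervention section stores the acquisitions of all newborns.
- **C2.** Age from a reliable last menstrual period is used only when available.

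The Data analysis section describes another random division of the database into two subsamples: "One of them to train the prediction model of GA", and the other to validate it. The protocol does not say whether this is the same division as the one for the secondary comparison.

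**The concern.** The secondary comparison asks how close the device comes to the early-ultrasound age, set beside the dating that would be available without that scan. Each infant should supply both errors, T-R and C1-R, so each can serve as its own control. Simulating an unknown R needs no random groups: R can be withheld while T and C are computed and then used to score both. A random division makes the result depend on the draw and widens its confidence interval, with no stated gain.

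The groups are also drawn from the complete database, which includes infants who may have trained the prediction model. For those infants T-R would be an in-sample error and C1-R would not.

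**Working it through.** **The protocol's own figure.** The plan states that "a sample of 787 subjects is necessary to detect an effect size of 10" per cent, and that "we assumed an alpha error of 0.05 and a power of test of 0.80 to support a paired t-test". Reading this as a standardised paired difference of 0.10, two-sided, the exact noncentral-t calculation gives n = 787 with power 0.8001, so the figure reproduces. The strata agree: 392 + 263 + 132 = 787. This calculation is for the within-infant primary endpoint and has no split in it.

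**Assumptions for the secondary comparison.** The protocol gives no allocation ratio, error SDs or error correlation. Assumed here: a 1:1 split; SDs of 11.0 days for T-R and 5.1 days for C1-R; zero-mean bivariate normal errors with signed correlation r between 0 and 0.4.

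**Why absolute errors.** Within an infant, (T-R) - (C1-R) = T - C1, so R cancels and the signed contrast only repeats the primary outcome. Closeness to R has to be judged on |T-R| and |C1-R|.

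**Layout A: T-R in one group, C1-R in the other.** Let a be the correlation between the two absolute errors.

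- Paired variance, all n infants: (vT + vC - 2a·sT·sC)/n.
- Split variance: (vT + vC)/(n/2).
- Ratio: 2(vT + vC)/(vT + vC - 2a·sT·sC). It does not depend on n. Taking absolute values multiplies both normal variances by the same constant, which cancels.
- Inputs: vT + vC = 121 + 26.01 = 147.01; 2·sT·sC = 2 × 11.0 × 5.1 = 112.2.
- Correlation of absolute errors: a = [√(1-r²) + r·arcsin(r) - 1]/(π/2 - 1).

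| Signed r | a | Ratio | 787 infants are worth |
|---|---|---|---|
| 0 | 0 | 294.02/147.01 = 2.00 | 787/2.00 ≈ 394 |
| 0.2 | (0.9798 + 0.0403 - 1)/0.5708 ≈ 0.035 | 294.02/(147.01 - 3.93) ≈ 2.05 | 787/2.05 ≈ 384 |
| 0.4 | (0.9165 + 0.1646 - 1)/0.5708 ≈ 0.142 | 294.02/(147.01 - 15.93) ≈ 2.24 | 787/2.24 ≈ 351 |

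The 2.00 at zero correlation does not depend on the SDs. It does depend on the 1:1 split. The best possible allocation for these SDs (11.0 to 5.1) gives (11.0 + 5.1)²/147.01 = 259.21/147.01 ≈ 1.76.

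**Layout B: all measures compared inside each group.** All pairing is kept, but each estimate rests on 393 or 394 infants. The variance doubles and the confidence interval is √2 ≈ 1.41 times as wide. As a yardstick, a paired t-test at a standardised difference of 0.10 has about 51% power in one half, against 80% in all 787. Reaching 80% in one half needs a standardised difference of about 0.141.

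**Training overlap.** The secondary outcome draws from the complete database. The Data analysis section trains a model on one random part of the same database. Neither section refers to the other or says which T values enter the secondary comparison. If T comes from the retrained model and training infants are included, T-R is partly in-sample. If T comes from a previously fixed model, or only validation infants are used, it is not.

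**The case against.** The strongest reply is that the layout of the comparison sits in a figure that cannot be seen. The text speaks of differences among R, T and the comparators, which fits a comparison of all of them inside each group. A condensed article may also leave the reason for the split to the full protocol. This stands as a limit: which measure goes in which group is inferred. It does not rescue the split, because both layouts lose precision.

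A reader might infer more than the text supports, in four ways:

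- **That all pairing is thrown away.** Even in Layout A, each error is still paired with its own R. Only the link between an infant's T error and C1 error is lost.
- **That at least half the information is certainly lost.** That needs a 1:1 split, which is not stated. For signed errors it also needs a non-negative correlation: at -0.3 with equal SDs the split keeps 65%. Non-negative is the likelier case, since both errors share the error in R, and absolute errors from zero-mean normal errors cannot correlate negatively.
- **That the variance ratio is 2.36 at correlation 0.2 and 2.88 at 0.4.** For absolute errors, these ratios hold only if 0.2 and 0.4 are correlations between the absolute errors themselves. As signed correlations they give 2.05 and 2.24.
- **That the comparison is biased towards the device.** A random split alone costs precision and causes no bias. Bias would need in-sample T values, and the protocol does not say that these are used.

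The reply that this is only a secondary comparison is also fair. It limits the weight of the point but is no reason to keep the split.

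**Conclusion.** The point holds as a matter of efficiency in a secondary analysis. The random two-group assignment is stated, no reason is given, and the design supplies R, T and C1 in every eligible infant, apart from missing data. The cost is about a doubling of variance: 2.0 to 2.24 times in Layout A under the assumptions listed, and 2.0 times in Layout B. Figure 1, the 1:1 ratio, the SDs and the correlations are all assumed.

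Possible use of in-sample T values is a gap to close and not a demonstrated bias. The primary agreement analysis (intraclass correlation, Bland-Altman plots, paired t-test) is within infants, so neither it nor N = 787 is touched.

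**What to change.** Drop the random two-group assignment for this comparison. Take every infant whose T is out-of-sample, meaning the validation subsample or cross-validated predictions. Compute T and C without using R, then score both against it:

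- |T-R| - |C1-R| in each of these infants;
- |T-R| - |C2-R| where C2 exists.

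Report the mean paired difference with a 95% confidence interval. State how this set relates to the training and validation subsamples in the Data analysis section. If the split serves a purpose that the article does not give, state it and confine the comparison to infants with an out-of-sample T.

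The cost is revised analysis wording and, if Figure 1 shows the two groups, a matching change there. No new data or additional infants are needed.

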**Figure 1 F1:**
[figure not shown]
Secondary outcome comparisons between the Reference-GA and the preemie-test in a simulated scenario without best pregnancy dating Legends: *Gestational age from crown-rump-length data adjusted to Intergrowth’s 21st fetal standard.^18^ R: reference. GA: gestational age. T, test; C1, comparator 1 is the GA calculated using the first ultrasound exam after 13 weeks and 6 days and before 22 weeks of gestation. C2, comparator 2 is the GA based on a reliable last menstrual period.

### The secondary outcome measures in the case–control nested study

Immediate complications, occurring during the first 72 hours of life due to pulmonary immaturity, are the secondary target. The outcome measures are as follows:To describe the relationship of the measurement of the newborn’s skin reflectance with RDS and with diagnoses based on clinical and radiological findings and respiratory outcomes.^6 19^To describe the relationship of the measurement of the newborn’s skin reflectance with the TTN and with diagnoses based on clinical findings and respiratory outcomes.^6^To describe the relationship of the measurement of the newborn’s skin reflectance with ventilatory support due to pulmonary immaturity.To describe the relationship of the measurement of the newborn’s skin reflectance with NICU admission due to RDS or TTN.

Time schedule of enrolment, intervention and outcome measurements are presented in a schematic diagram (see figure 2). The assessment occurs during the first 24 hours of life, but participants will be followed-up for 72 hours or until discharge or death, whichever occurs first, for the monitoring of neonatal outcomes and adverse events.

**Figure 2 F2:**
[figure not shown]
Participant timeline of the study GA, gestational age; LMP, last menstrual period; R, reference.

### Sampling and sample size

The sample size calculation is estimated based on the primary endpoint. To test the hypothesis of equivalence between the preemie-test GA and the comparators GA, a sample of 787 subjects is necessary to detect an effect size of 10%. Using the G-Power 3.1 software,^20^ we assumed an alpha error of 0.05 and a power of test of 0.80 to support a paired t-test.

Sampling intends to arrange three groups of GA enrolment to preserve enough premature newborns with 3:2:1 proportion, similar to Wilson *et al*^21^: 392 term newborns, 263 premature newborns from 32 to 36 weeks and 6 days of GA and 132 extremely premature newborns from 24 to 31 weeks and 6 days of GA.

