### Primary outcome measures

The primary target is the agreement between the GA offered by the preemie-test (T) and the GA calculated by the comparators (C1 and C2), so as to perform the new test in scenarios without the Reference-GA (R). The outcome is the difference between the GA calculated by the photobiological neonatal skin assessment methodology in relation to the age calculated by the comparators.

Another measure for the primary target is the detection of preterm newborns, considering the age before 37 weeks of pregnancy as the threshold between term and preterm births, and analysing sub-categories of preterm birth, based on GA^4^:Extremely preterm (<28 weeks).Very preterm (28–32 weeks).Moderate to late preterm (more than 32 to <37 weeks).

In this case, the outcome is the proportion of the preterm newborn correctly detected at birth, based on the photobiological test of the skin, within a 1-week error.

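### The hypothesis is equivalence, but 787 is the sample size for detecting a difference with a paired t-test, so the stated 80% power does not belong to the stated hypothesis and no margin is given

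*Protocol article*

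**What the plan says.** Under Sampling and sample size, the protocol article states: "To test the hypothesis of equivalence between the preemie-test GA and the comparators GA, a sample of 787 subjects is necessary". The same sentence sizes the trial "to detect an effect size of 10" per cent, and the next one says "we assumed an alpha error of 0.05 and a power of test of 0.80 to support a paired t-test", using G-Power 3.1. It does not say whether the test is one- or two-sided.

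Under Data analysis, the primary endpoint is analysed by an intraclass correlation coefficient, Bland-Altman plots "and paired t-testing", with a 5% significance level and 95% confidence intervals. The paired t-test is the only hypothesis test named for the gestational age (GA) difference. The same section divides the database at random into one part that trains the GA model and another that validates it, without giving the sizes.

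Under Primary outcome measures, the only tolerance is "within a 1-week error", and it applies to the detection of preterm newborns, not to the GA difference.

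**The concern.** An equivalence hypothesis and a paired t-test point in opposite directions. The t-test takes zero mean difference as its null hypothesis and gathers evidence against it. Equivalence takes a difference at least as large as some margin as its null. Failing to reject the first does not reject the second.

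Two things follow:

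- The 80% power describes the chance of detecting a mean difference of 0.1 SD. It is not the chance of demonstrating equivalence, which cannot be calculated until a margin exists.
- If a non-significant t-test were offered as support for equivalence, it would speak only to the average error. A clinician using the device on one newborn needs to know the spread of individual errors. A wide spread inflates the standard error, so it makes non-significance more likely.

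The article describes the device as being in the pivotal phase on the way to regulatory approval, so the primary inference and its justification should refer to the same hypothesis.

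**Working it through.** **Inputs from the protocol article.** Sample size 787, effect size 10%, alpha 0.05, power 0.80, paired t-test (Sampling and sample size). The effect size is read as 0.1 SD of the paired differences.

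**1. Reproducing 787.** Power of a two-sided paired t-test from the noncentral t distribution, with noncentrality 0.1 × √n and n − 1 degrees of freedom:

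- n = 786: power 0.7996
- n = 787: power 0.8001

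So 787 is the smallest n that reaches 0.80. A one-sided test would need 620, so the calculation was two-sided. The figure is correct for a difference test.

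**2. What non-significance shows at n = 787.** The critical t is 1.963, and 1.963/√787 = 1.963/28.05 = 0.070. Non-significance means that the observed mean difference is below 0.070 SD in size. Its 95% confidence interval then lies within about ±(0.070 + 0.070) = ±0.14 SD. This bounds the mean bias in SD units and places no limit on the SD.

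**3. Effect of noise.** Take a true mean bias of 1 day and n = 787, with assumed SDs of the differences:

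| SD of differences | Bias in SD units | Chance the t-test is significant |
|---|---|---|
| 0.5 week | 1/3.5 = 0.286 | almost 100% |
| 1.83 weeks | 1/12.81 = 0.078 | 59% |
| 4.4 weeks | 1/30.8 = 0.032 | 15% |

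With the same bias, the noisiest device is the least likely to be flagged.

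**4. Power for equivalence.** No margin is stated. If ±0.1 SD is taken as the margin (an assumption) and the true bias is zero, two one-sided tests have power of about 2Φ(0.1√n − t) − 1, where t is the one-sided critical value:

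- n = 787, 5% each side: 2Φ(2.805 − 1.647) − 1 = 0.75
- n = 787, 2.5% each side: 2Φ(2.805 − 1.963) − 1 = 0.60
- n for 80% power: 858 (5% each side) or 1,053 (2.5% each side)

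If half the infants are held out for validation (assumed, n = 394), the 5% figure is 2Φ(1.985 − 1.649) − 1 = 0.26.

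**5. A margin in time units.** The requirement is approximately (1.645 + 1.282)² × (SD/margin)². Over assumed SDs of 1 to 4 weeks:

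- 1-week margin: 9 to 138 infants
- 3-day margin: 47 to 747 infants
- 1-day margin: 420 to 6,715 infants

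Whether 787 is large or small depends entirely on the missing margin and SD.

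**6. Precision of the limits of agreement.** The 95% half-width for each limit is 1.96 × √(1/n + 1.96²/(2(n − 1))) SD:

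- n = 787: 1.96 × √(0.00127 + 0.00244) = 0.12 SD
- n = 394: 1.96 × √(0.00254 + 0.00489) = 0.17 SD

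**The case against.** The strongest reply is that the t-test does not stand alone. The article lists the intraclass correlation and Bland-Altman plots before it, plans a separate accuracy analysis for prematurity with a 1-week margin, and nowhere says that a non-significant t-test counts as success. Acceptance limits may be in a fuller protocol or analysis plan. All of this stands, and it rules out three stronger readings:

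- **That a device with no information would pass the trial.** It could survive the t-test if it were right on average. With GA assumed uniform within the three enrolment groups (SD about 4.4 weeks), a constant equal to the training-half mean was non-significant in about 85% of simulated trials. The other planned analyses would expose it: limits of agreement for a constant would be about 1.96 × 4.4 = ±8.6 weeks, and the intraclass correlation of a random guess is about 0. A constant that was off by half a week would be non-significant only about 11% of the time with all 787 infants.
- **That the mean error is near zero by construction because the model is trained on the same database.** The article does not say which GA trains the model. The primary comparison is with the 14-to-22-week ultrasound and the last menstrual period. If the earlier reference ultrasound is the training target, any systematic gap between the dating methods carries into the tested difference.
- **That a non-significant result shows nothing, or that 787 is too small.** Steps 2 and 5 above contradict both.

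The reply leaves the mismatch itself untouched. The article fixes the hypothesis, test, alpha, power and sample size, and they do not fit together. This is a contradiction in the text, not detail left to another document.

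**Conclusion.** The point holds in this limited form. The sample size is correct for a two-sided paired t-test to detect 0.1 SD, but the stated hypothesis is equivalence, so the 80% power is claimed for a hypothesis that the calculation does not address. No margin is given. A non-significant t-test would bound the mean bias at about ±0.14 SD when all 787 infants are analysed. It would not show individual agreement, and it would come more easily with a noisier device. The analyses that do address individual agreement are planned, but they do not carry the sample-size justification.

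The reproduction of 787 rests only on reading 10% as 0.1 SD and the test as two-sided, and the exact match supports both. The equivalence power of 75% depends on taking ±0.1 SD as the margin, zero true bias, 5% each side and all 787 infants evaluating the device. It falls to about 26% if half are used to train the model, a split that the article does not state.

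**What to change.** 1. Stop using the paired t-test as evidence of agreement.
2. Test the mean difference with two one-sided tests, or require its confidence interval to lie within a margin. Fix that margin in days, with a clinical reason, before the data are seen.
3. Make the already planned Bland-Altman limits of agreement, with confidence intervals, and the share of infants within 7 days the main evidence of agreement. The 7 days match the 1-week tolerance already used for preterm detection.
4. Keep enrolment at 787, but remove the claim of 80% power for equivalence. Restate the justification as precision for the infants who actually evaluate the preemie-test, and state the size of that subsample. The figures are about ±0.12 SD per limit for all 787, or about ±0.17 SD if about half are held out. If equivalence power is also quoted, give it for the same infants and the chosen margin.

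The cost is rewording in the sample-size and analysis sections and the work of choosing a margin. No extra patients are needed for the precision-based justification. The stated power or precision will look less favourable than at present, markedly so if only part of the sample evaluates the device.

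### The power of 0.80 needs all 787 infants in the paired test, but the same 787 are also split to train the gestational-age model, with no allowance for this in the sample size

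*Protocol article*

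**What the plan says.** Under Sampling and sample size, the protocol article ties the number of infants to the primary endpoint: "a sample of 787 subjects is necessary to detect an effect size of 10" per cent. For the error rates it says "we assumed an alpha error of 0.05 and a power of test of 0.80 to support a paired t-test". It then divides enrolment into three gestational-age groups: "392 term newborns, 263 premature newborns from 32 to 36 weeks and 6 days of GA and 132 extremely premature newborns".

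Under Data analysis, the modelling paragraph says that "computational randomisation will select two subsamples in the database". One subsample trains the prediction model on skin reflectance and clinical variables. For the remainder it says: "Another part will be for the analytical validation of the predictive model". The same paragraph plans to improve the existing models. The next paragraph lists the primary analyses (intraclass correlation, Bland-Altman plots, paired t-tests, accuracy for prematurity within one week) and does not say which infants enter them.

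**The concern.** The same 787 infants appear to be counted twice: once in full as the sample for the paired test, and again as a training part plus a validation part. Only infants outside the training part have a preemie-test age that was not fitted to their own data. A validation study should therefore be sized on them.

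Two things are at stake. An out-of-sample paired test would not have the power that the article states. The other primary measure, detection of preterm birth, would rest on fewer preterm infants than the quotas were designed to secure, with the largest loss of precision in the smallest group.

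**Working it through.** **Inputs.** From Sampling and sample size: n = 787, effect size 10% (read as a standardised paired difference d = 0.10), alpha 0.05, power 0.80, and quotas of 392, 263 and 132. From Data analysis: a random split into two parts, with no ratio given. The validation share is therefore an assumption and is shown as a range.

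**Step 1: reproduce 787.** Power of a two-sided paired t-test is P(|t'| > t(0.975, n−1)), where t' is non-central t with n−1 degrees of freedom and non-centrality d√n. At n = 787, the non-centrality is 0.10 × √787 = 2.805, the critical value is 1.963 and the power is 0.800. At n = 786 power is just under 0.80. A one-sided 5% test would need 620. The stated figure is therefore two-sided with d = 0.10, and it uses all 787 pairs.

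**Step 2: look for a surplus.** 392 + 263 + 132 = 787. No infants are added for model training.

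**Step 3: power on the validation part alone.** The formula is the same, with d = 0.10. The last column solves for the d that gives power 0.80.

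| Assumed validation share | n | Power at 0.10 SD | SD detectable with power 0.80 |
|---|---|---|---|
| 80% | 630 | 0.71 | 0.112 |
| 70% | 551 | 0.65 | 0.120 |
| 50% | 394 | 0.51 | 0.141 |
| 30% | 236 | 0.33 | 0.183 |
| 20% | 157 | 0.24 | 0.225 |

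Power reaches 0.50 at n = 387, which is 387/787 = 49% of the sample. Since 787 is the smallest n that reaches 0.80, every split falls short. To keep 787 in validation, enrolment would have to be 787/0.5 = 1574 for an even split, or 787/0.3 = about 2624 for a 30% share.

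**Step 4: preterm detection.** The 95% half-width is 1.96 × √(p(1−p)/n). Take p = 0.90 as an illustration (the article gives no expected value) and an even split. For all preterm infants, 263 + 132 = 395 gives 3.0 percentage points and 198 gives 4.2. For those below 32 weeks, 132 gives 5.1 and 66 gives 7.2.

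**Step 5: what if all 787 are tested?** Assume a least-squares model with an intercept. The mean residual in the training infants is then zero by construction, so these infants carry no information on the device's mean error against the age it was trained on.

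**Step 6: a caveat on step 3.** The powers apply to the model held fixed after training. Error in the trained intercept is shared by every validation infant. With an even split this makes the variance of the mean error, over repeated training, about 1/394 + 1/393 instead of 1/394 (in units of the residual variance). The true standard error is then about √2 times the nominal one. A nominal 5% test of a modelling procedure with no bias would reject with probability 2 × (1 − Φ(1.96/√2)) = 0.17. Simulations with five predictors gave 15% to 17%.

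**The case against.** The strongest reply is that the article never confines the primary test to the validation part. The split stands in a paragraph about modelling, and the primary-endpoint paragraph names no subset. A model already exists: the Introduction reports one from the feasibility study with R² = 0.828, and the Intervention section describes a prototype that hides its predicted age from the examiner. A model of that kind, locked, could be tested on all 787 with the stated power. The split ratio and analysis set may also be in a fuller document that is not shown.

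Much of this stands. A reader might infer that power is simply about one half or less. The documents do not support that: it requires a validation share of no more than about half, and at 70% or 80% power is 0.65 or 0.71. Nor is a missing ratio a fault in a condensed article.

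The conflict remains, however. The article states both the sample size and the split, and the first leaves no room for the second. Nothing says that a locked model supplies the primary result, and the planned improvement of the models points the other way.

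Two further limits are fair. First, the loss is modest in absolute terms. With an assumed SD of differences of 1 to 2 weeks, the detectable difference at an even split moves from 0.7–1.4 days to 1.0–2.0 days. Second, the declared aim is "To test the hypothesis of equivalence between the preemie-test GA and the comparators GA", and power to detect a difference is not power to show equivalence. Restating the first does not settle the second, which is a separate matter.

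**Conclusion.** The point holds in a conditional form. The calculation of 787 is correct in itself, but it applies to 787 pairs, and the analysis plan uses an unstated part of the same infants to train the model. If the primary comparison uses only infants not used for fitting, power at 0.10 SD is below the stated 0.80 whatever the split: 0.71 at an 80% validation share, 0.51 at an even split, 0.33 at 30%. If it uses everyone, the nominal number is kept but independence from model fitting is lost. Only a model locked before enrolment would give both, and the article does not commit to one.

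The power figures rest on a two-sided test, an effect of 0.10 SD, the assumed shares and a model held fixed after training. The preterm half-widths also rest on the illustrative 0.90.

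**What to change.** Amend Sampling and sample size and Data analysis together, by one of two routes.

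1. State that the primary agreement and preterm-detection analyses use only infants not used to train or tune the model. Fix the split ratio in advance. Replace the claim of 0.80 power with 787 by the power and detectable difference for the validation part. For an even split this would read: 394 infants, power 0.51 at 0.10 SD and 0.80 at 0.14 SD, for a model held fixed after training.
2. Make the primary test an evaluation of the feasibility-study model, locked before enrolment, on all 787 infants, and keep 0.80. Any model improved on the trial data is then secondary.

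Pooled k-fold cross-validation should not be used to restore 787 for the paired t-test. The pooled out-of-fold mean error is close to zero by construction. In simulations of 10-fold least squares with 787 infants, five predictors and residual SD 1, it had an SD of 0.001 against a nominal standard error of 1/√787 = 0.036, and the test rejected in none of 1000 runs.

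Both routes are changes of wording and need no extra infants. The first costs a less favourable stated power. The second means that the improved model is not the one formally tested. The choice should be fixed before the data are analysed.
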